## Abstract

**Background:**

The presence of depressive subsyndromal symptoms (SS) in bipolar disorder (BD) increases the risk of affective relapse and worsens social, cognitive functioning, and quality of life. Nonetheless, there are limited data on how to optimize the treatment of subthreshold depressive symptoms in BD. Mindfulness-Based Cognitive Therapy (MBCT) is a psychotherapeutic intervention that has been shown effective in unipolar depression. The assessment of its clinical effectiveness and its impact on biomarkers in bipolar disorder patients with subsyndromal depressive symptoms and psychopharmacological treatment is needed.

**Methods/design:**

A randomized, multicenter, prospective, versus active comparator, evaluator-blinded clinical trial is proposed. Patients with BD and subclinical or mild depressive symptoms will be randomly allocated to: 1) MBCT added to psychopharmacological treatment; 2) a brief structured group psychoeducational intervention added to psychopharmacological treatment; 3) standard clinical management, including psychopharmacological treatment. Assessments will be conducted at screening, baseline, post-intervention (8 weeks) and 4 month follow-up post-intervention. The aim is to compare MBCT intervention *versus* a brief structured group psychoeducation. Our hypothesis is that MBCT will be more effective in reducing the subsyndromal depressive symptoms and will improve cognitive performance to a higher degree than the psychoeducational treatment. It is also hypothesized that a significant increase of BDNF levels will be found after the MBCT intervention.

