The brain -derived neurotrophic factor (BDNF) is a dimeric protein that promotes the growth and maintenance of neuronal connections, modulates neurotransmission and participates in the mechanisms of learning and long-term plasticity (LTP). Peripheral BDNF in serum and plasma can be assessed noninvasively by venipuncture. Since it crosses the blood–brain barrier, its levels in serum and plasma are highly correlated with levels in cerebrospinal fluid (r ¼ 0.8) [37,38]. There are numerous studies assessing peripheral levels of BDNF in bipolar disorder patients. Some studies suggest that BDNF levels decrease during mood acute states and remain normal during euthymia, but other studies have contradicted this paradigm. A recent meta-analysis has measured the effect sizes of the differences in BDNF levels between BD patients in different mood states and controls. The BDNF levels were decreased in both mania and depression when compared to controls [39,40] but were not different in euthymia [41]. Meta-regression analyses in euthymia showed that age and length of illness influenced the variation in effect sizes [42]). BDNF levels are consistently reduced during manic and depressive episodes and recover after treatment for acute mania, so peripheral BDNF could be used as a biomarker of mood states and disease progression for BD.

In summary, the presence of persistent depressive subthreshold symptoms increases the risk of affective relapse and negatively affects the prognosis of BD. However, there is no an evidence-based specific treatment for them. MBCT appears as a promising intervention, since it has been found to be effective in reducing current depressive symptoms in MDD [23,43]. Our objective is to evaluate the efficacy of the MBCT added to standard drug treatment -following the recommendations of the Spanish Guideline for the Treatment of BD [11])- *versus* structured group psychoeducation versus standard clinical management. Our primary outcome is reduction of residual depressive symptoms. Secondary outcomes are manic and anxiety symptoms, recurrence, cognitive and social functioning and levels of BDNF.

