## Discussion

This study will provide feasibility information and preliminary effect size estimates to inform the effectiveness of adjunctive MBCT, adjunctive group psychoeducation and standard treatment on SS or mild depressive symptoms in BD. It is of interest to researchers involved in the development of new approaches to the treatment of residual affective symptoms and its negative impact in the course of illness. It can also provide information on variations of BDNF in the different treatment arms and on neuropsychological measures, which might suggest mechanisms of action and differences among treatments.

Strengths of the study include targeting a defined sample of bipolar patients with persistent depressive symptoms despite receiving a correct pharmacological treatment. This sample –as reported before- is representative of a high percentage of bipolar out-patients, who remain symptomatic more than one third of the time. The trial protocol was registered before randomization began (ClinicalTrials.gov: NCT02133170 Registered 04/30/2014) and was developed according to good clinical research practice enabling the randomized trial to be conducted with low risk of bias and a high degree of external validity. Both MBCT and psychoeducational interventions will be conducted using manuals and adherence to the treatment manuals will be tested. This makes it possible to implement the interventions in clinical practice, and the two interventions can be assessed in future trials. To standardize the application of MBCT and psychoeducation, specific training and meetings will be held. Specific training also may increase the inter-rater reliability on scales.

Since an 8-week psychoeducational program based in the Barcelona group-structured model has not proved effective neither in depressive symptoms nor in episode prevention, this could be a study weakness. But our objective is to compare MBCT versus an active psychosocial intervention, and this is the best model we could find. Sample size could also be a limitation, as well as the time of follow-up, especially regarding the possible effects on long-term course of BD.

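### The BDNF hypothesis is worded as a rise after MBCT with no comparator, so a rise shared by all arms would satisfy it without any MBCT-specific effect

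*Protocol article*

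**What the plan says.** The Methods/design paragraph of the abstract gives the aim as a comparison: "The aim is to compare MBCT intervention *versus* a brief structured group psychoeducation". The clinical hypotheses follow that form; MBCT is expected to reduce depressive symptoms more and "will improve cognitive performance to a higher degree than the psychoeducational treatment". The next sentence drops the comparator: "It is also hypothesized that a significant increase of BDNF levels will be found after the MBCT intervention".

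Other sections bear on BDNF as follows.

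- **Methods/design (main text):** all three groups are assessed, and BDNF is among the variables listed.
- **Secondary endpoints:** BDNF is defined as change from baseline to visit 1, with no contrast named.
- **Data analysis:** change in the primary and secondary outcomes is analysed by repeated-measures ANOVA, without saying which effect (time, or group by time) answers which hypothesis. Tests are two-sided at 0.05.
- **Background:** the rationale is that "BDNF levels are consistently reduced during manic and depressive episodes and recover after treatment for acute mania". On this basis the article proposes blood levels as a marker of mood state. The same paragraph also says that other studies contradict the mood-state pattern, and that levels in euthymia did not differ from controls.
- **Discussion:** BDNF and neuropsychological data are expected to inform on the treatment arms, "which might suggest mechanisms of action and differences among treatments".

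**The concern.** A change from before to after treatment in one arm of a randomised trial mixes the effect of the treatment with everything else that happens over eight weeks: natural course, regression to the mean after selection on HDRS 8–19, continuing medication, and assay or seasonal drift. The comparator arms are there to remove these, and BDNF is measured in them, but the hypothesis does not use them.

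At stake is what a positive BDNF result would mean. If levels rose equally under MBCT, psychoeducation and TAU, the hypothesis as written would be met. Yet there would be no evidence that MBCT affects the biomarker, and no support for the reading about mechanisms and differences among treatments that the Discussion looks for.

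**Working it through.** The article states no power, effect size, mean or SD for BDNF, so there is no figure of its own to reproduce. The calculation below is illustrative.

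**Inputs from the article.** N = 140 (Subjects); allocation 2:2:1 (Methods/design); two-sided 0.05 (Data analysis). Arm sizes are 140 × 2/5 = 56 for MBCT, 56 for psychoeducation, and 140 × 1/5 = 28 for TAU.

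**Assumptions (not in the article).** BDNF rises by the same amount d in every arm, in units of the SD of the change, so MBCT has no specific effect. Changes are normal with equal SD. All randomised patients are analysed, except in the last column of the first table.

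**Step 1: within-arm reading.** The paired t statistic in MBCT has non-centrality d√n. With n = 56, √56 = 7.483, and the probability of a significant rise is the upper tail of the non-central t with 55 df beyond its 97.5% critical value.

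| Common shift d | d√56 | P(significant rise), n = 56 | P(significant rise), n = 45 (assumed loss of about 20%) |
|---|---|---|---|
| 0.2 | 1.50 | 0.312 | 0.259 |
| 0.3 | 2.24 | 0.597 | 0.503 |
| 0.4 | 2.99 | 0.837 | 0.747 |

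With no shift (d = 0) the figure is 0.025.

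**Step 2: between-arm reading of the same situation.** The shift cancels in the difference in mean change, (d) − (d) = 0. A two-sided 5% test therefore favours MBCT over psychoeducation 2.5% of the time, whatever d is. A simulation of 20,000 trials at each of d = 0.2, 0.3 and 0.5 gave 2.5%, 2.6% and 2.6%. The three-arm group-by-time test was significant in 5.0% to 5.1% of trials.

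**Step 3: what the between-arm test costs in sensitivity.** The difference detectable at 80% power, by normal approximation with 1.960 + 0.842 = 2.802, is:

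| Contrast | Formula | Detectable, SD of change |
|---|---|---|
| Within MBCT | 2.802 / √56 | 0.37 |
| MBCT v psychoeducation | 2.802 × √(2/56) | 0.53 |
| MBCT v TAU | 2.802 × √(1/56 + 1/28) | 0.65 |

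**The case against.** The strongest reply is that one sentence in an abstract is a hypothesis and not an analysis specification, and that the rest of the article already leans towards a comparison. The stated aim is comparative, BDNF is collected in all arms, the repeated-measures model can test group by time, and the Discussion speaks of differences among treatments. No section prescribes a paired test in the MBCT arm, and a condensed article may leave the choice of model effect to a fuller document. This stands as far as it goes: the design and the planned model can deliver the right contrast. It does not remove the point, because the hypothesis itself is stated, and stated in a form that differs from the ones beside it and cannot carry the intended conclusion.

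Four stronger readings are tempting and are not supported.

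- **A reader might infer that recovery in any arm would confirm the hypothesis.** It would not. The wording requires a rise after MBCT; a rise confined to psychoeducation or TAU fails it. The problem arises when a rise is shared.
- **A reader might infer that the article predicts such a shared rise.** The Background is hedged. Its reductions concern manic and depressive episodes, and its statement that levels "recover after treatment for acute mania" does not extend to depression. This trial excludes acute episodes in the prior 12 weeks, and the Background gives no BDNF result for subsyndromal symptoms.
- **A reader might take age and length of illness as necessary covariates.** The source sentence reads "Meta-regression analyses in euthymia showed that age and length of illness influenced the variation in effect sizes". It concerns variation in effect sizes in euthymia, not change within patients over eight weeks.
- **A reader might take 31% to 84% as the error rate of the planned analysis.** These figures belong to a paired test that the article does not name, under shifts that it does not give.

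**Conclusion.** The point holds as one about the wording of a hypothesis, not about the design or the data collection. The BDNF hypothesis lacks the comparator that the aim and the neighbouring hypotheses have, and nothing else in the article supplies it. Any change over time common to the arms would meet it; this logic does not depend on the mood-state evidence or on the size of the shift.

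The size is conditional: about 31% to 84% apparent confirmation within MBCT for an assumed common shift of 0.2 to 0.4 SD with 56 analysed, against 2.5% for a between-arm result favouring MBCT. With no common shift the two readings carry the same 2.5%, so the practical harm depends on an unknown quantity. BDNF is a secondary outcome in a trial that calls itself a pilot, and the primary depression comparison is untouched. The change should be made, but nothing central depends on it.

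**What to change.** Restate the hypothesis as: the change in BDNF from V0 to V1 will be greater with MBCT than with psychoeducation. Name the contrast that tests it, namely the group-by-time contrast for these two arms and these two visits in the planned repeated-measures model, and report the estimate with a 95% CI. The difference in change adjusted for baseline BDNF is an acceptable alternative that targets the same between-arm effect under randomisation. Show TAU as context, and report the change within MBCT descriptively, without a test that decides the hypothesis.

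Adjustment for age and length of illness, and a model that includes concurrent HDRS change, are optional. If the latter is run it should be labelled exploratory, since it conditions on a variable measured after randomisation.

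The cost is one sentence and one named contrast, on samples already planned in all three arms. The real downside is sensitivity: the difference detectable at 80% power rises from about 0.37 to 0.53 SD of the change, so a smaller MBCT-specific effect on BDNF may well go undetected.

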**Discussion:**

This is the first randomized controlled trial to evaluate the effects of MBCT compared to an active control group on depressive subthreshold depressive symptoms in patients with bipolar disorder.

**Trial registration:**

ClinicalTrials.gov: NCT02133170. Registered 04/30/2014.

## Background

Even in environments with standard psychiatric treatment and regular follow-up, around 38% of patients who have recovered from an acute episode of bipolar disorder (BD) show persistent subthreshold symptoms (SS) [1]. The Depression Comorbidity Study shows that the time with SS is higher than time in episode throughout the follow-up, with a clear predominance of depressive SS [2]. In a Spanish cohort, patients were symptomatic for one third of the 72-weeks follow-up, and also one third of the visits. In addition, they spent three times more days depressed than manic or hypomanic [3]. The persistence of SS has been associated with an increased risk of affective relapse/recurrence [4-6], a shorter time to relapse [7], greater functional impairment − similar to that experienced by patients with depressive episode−, worse quality of life, delayed functional recovery [8,9]) and poorer cognitive performance [10].

Nevertheless, few studies have assessed the efficacy of treatments on bipolar patients with depressive SS. Evidence of effectiveness using only drugs is limited, therefore alternatives are needed. Concomitant psychosocial interventions are recommended, such cognitive behavioral therapy (CBT), interpersonal and social rhythm therapy (IPSRT) and structured psychoeducation, especially for stabilization between episodes and relapse prevention [11]. In a recent study, a 21-session individual CBT was shown as effective -but much less cost-effective- as a brief psychoeducational group intervention, with overall decrease in disease burden, effectiveness in preventing episodes and time to relapse [12]. A combined treatment (pharmacological *plus* psychoeducational and cognitive-behavioral therapy) has shown to decrease depressive symptoms, even in refractory BD, and the number of hospitalizations [13]. Despite psychoeducational interventions appear to be most promising, the development of effective psychosocial therapies is still needed.

Mindfulness and acceptance-based interventions (MABIs) are receiving increasing attention in the treatment of mental disorders and show promise for symptoms of anxiety and depression both in clinical and nonclinical populations [14]. The practice of mindfulness works well in cognitive processes (rumination, cognitive reactivity, experiential avoidance), which have been associated with vulnerability to depressive and anxious symptoms and neuropsychological performance [15]. Mindfulness is currently defined in psychological terms as “paying total attention to the present moment with a non-judgmental awareness of inner and outer experiences” [16]. The primary mechanism of action is the moment-by-moment attention of our thoughts, feelings, bodily sensations, and surrounding environment, which promotes emotional regulation and awareness of the basic processes influencing the attribution of meaning to experiences. As important as the attention training is the promotion of an attitude of openness, curiosity and acceptance of all the experiences that arise. Mindfulness-Based Cognitive Therapy (MBCT), developed by Segal, Williams and Teasdale [17] is a group-based, 8-week, mind-body intervention that integrates psychological educational aspects of CBT for depression with meditation components of mindfulness-based stress reduction developed by Kabat-Zinn [16]). It has proven effective as adjunctive therapy in preventing relapse of recurrent depressive disorder [18-21] and reducing the residual depressive symptoms in unipolar depression [22,23]. In a pilot trial, MBCT compared to psychoeducation was significantly more effective in improving subsyndromal depressive symptoms in patients with unipolar depression [24]. In addition, MBCT is recommended in the NICE (National Institute for Health and Clinical Excellence) clinical guideline for the treatment of unipolar depressive patients with a history of 3 or more episodes [25].

Some preliminary studies and a randomized controlled trial with a long follow-up have examined MBCT in the treatment for bipolar disorder. Williams et al. [26] conducted a pilot clinical trial evaluating the effectiveness of MBCT versus waitlist on between-episode anxiety and depressive symptoms. Although the results were favorable for MBCT, these should be analyzed with caution given the small size and heterogeneity of the sample. Miklowitz et al. [27] studied the effect of a modified MBCT protocol with two additional treatment elements specifically designed for patients with bipolar disorder: psychoeducation about mood changes and its provoking factors (e.g. interpersonal conflict, sleep/wake cycle disruptions) and upon identification of these factors bringing mindfulness to prodromal signs of mood elevation. Small to medium effect sizes for improvement in depression and anxiety symptoms in remitted patients with bipolar disorder were found. In other preliminary study, at the end of a MBCT treatment, as well as at the 3-month follow-up, participants with BD showed lower residual depressive mood symptoms, less attentional difficulties, increased emotion-regulation abilities, psychological well-being, more positive affect, and psychosocial functioning and improvements in executive functioning, memory, and ability to initiate and complete tasks [28]. Other controlled studies have also shown a beneficial effect of MBCT for patients with BD, but with limitations such as small sample, absence of randomization or of an active comparator [29,30]. Perich et al. [31] have compared MBCT plus treatment as usual (TAU) to TAU alone in a RCT over a 12 month follow-up period. MBCT did not lead to significant reductions in time to depressive or hypo/manic relapse, total number of episodes, or mood symptom severity at 12-month follow-up; however, there was some evidence for an effect on anxiety symptoms. Despite decreases in depression were only observed at a trend level, further research is required to analyze the effect of MBCT on residual depressive symptoms in bipolar patients.

Mindfulness-based interventions are cost-effective, showing a potential to significantly reduce societal costs and increase the effectiveness of care [32]. Research in this field has shown important methodological limitations: differences in the application of the MBCT intervention, both in duration and number of sessions or the amount of incorporated psychoeducational elements; the limited statistical power due to small sample size; lack of control for possible confounding factors such as pharmacological treatment, or lack of information on the severity of the disease; and scarcity of long-term randomized clinical trials that allow to assess the maintenance of achieved effects. In the present project we try to overcome several of these limitations, especially by using the method of randomized clinical trial with an active comparator, the larger sample size and the attempt to control confounding variables regarding the condition and design of the intervention.

Structured group psychoeducation is an adjunctive psychological treatment that has been shown to be effective in the prevention of affective recurrences as well as number of hospitalizations and time with symptoms in BD euthymic outpatients, both at two-year [33] and five-year follow-up [34]. This psychoeducational program is structured in 21 sessions delivered through 6 months. It stresses the importance of illness awareness, self-management, early-warning sign identification, habit regularity, treatment adherence and avoiding drug misuse. “It has been defined as “behavioural psychoeducation”, but its authors rather think of it as an “attitudes & aptitudes” psychoeducational program. This definitely corresponded to a view of bipolar disorder as a complex condition involving not only biological etiological factors but also psychological and social variables that may act as triggering factors, modulators or mediators” [35]. This study has been successfully replicated in pharmacologically treated patients with bipolar disorder also in routine clinical settings [36].

The brain -derived neurotrophic factor (BDNF) is a dimeric protein that promotes the growth and maintenance of neuronal connections, modulates neurotransmission and participates in the mechanisms of learning and long-term plasticity (LTP). Peripheral BDNF in serum and plasma can be assessed noninvasively by venipuncture. Since it crosses the blood–brain barrier, its levels in serum and plasma are highly correlated with levels in cerebrospinal fluid (r ¼ 0.8) [37,38]. There are numerous studies assessing peripheral levels of BDNF in bipolar disorder patients. Some studies suggest that BDNF levels decrease during mood acute states and remain normal during euthymia, but other studies have contradicted this paradigm. A recent meta-analysis has measured the effect sizes of the differences in BDNF levels between BD patients in different mood states and controls. The BDNF levels were decreased in both mania and depression when compared to controls [39,40] but were not different in euthymia [41]. Meta-regression analyses in euthymia showed that age and length of illness influenced the variation in effect sizes [42]). BDNF levels are consistently reduced during manic and depressive episodes and recover after treatment for acute mania, so peripheral BDNF could be used as a biomarker of mood states and disease progression for BD.

In summary, the presence of persistent depressive subthreshold symptoms increases the risk of affective relapse and negatively affects the prognosis of BD. However, there is no an evidence-based specific treatment for them. MBCT appears as a promising intervention, since it has been found to be effective in reducing current depressive symptoms in MDD [23,43]. Our objective is to evaluate the efficacy of the MBCT added to standard drug treatment -following the recommendations of the Spanish Guideline for the Treatment of BD [11])- *versus* structured group psychoeducation versus standard clinical management. Our primary outcome is reduction of residual depressive symptoms. Secondary outcomes are manic and anxiety symptoms, recurrence, cognitive and social functioning and levels of BDNF.

